**Dosing regimen:**

**Intervention Arms (Arms 1, 2, 3, 4, 5):** Participants allocated to PVP-I solution (especially prepared for the study) after confirmation of COVID-19 positivity. Proper dilution with normal saline will be added, which will be physically and chemically stable for 6 hours. Other supporting care (crystalloid solution infusion), and monitoring of vital statistics, in case of bleeding protective measures will be performed according to the national guidelines.

**Control Arms (Arms 6 and 7):** Participants allocated distilled water for nasal irrigation for Arm 6 a placebo that will also be reconstituted and applied at the same rate as mentioned in the invention groups and distilled water for nasal spray for Arm 7 a placebo that will also be reconstituted and applied at the same rate as mentioned in the invention groups.

In both Arms of patients, 10 ml of PVP-I or distilled water will be administered for 2 minutes. Nasal spray will be administered in each nostril using an atomizing device (2 sprays for average device). Control groups, will receive distilled water irrigation and distilled water nasal spray at similar amounts and durations. Further RT-PCR will be assessed within 1 minutes to 15 minutes of the following intervention.

**Participant compliance:** The study team will not create any problem with compliance while the patient is under care and supervision in the hospital. It will be ensured that all recruited patients will receive the appropriate interventions, although they could be interrupted due to the onset of potential adverse effects such as hypotension.

**Overdose:** The study team will titrate the drugs against the key adverse effect of hypotension. Nasal spray and nasal irrigation will be halted if patients complain of significant discomfort or clinically significant hypotension or signs of anaphylaxis. Procedures will be started again at a lower rate if the condition settles or according to the patient’s choice.

**Responsibility sharing of care of the patients:** As the patients will remain under the care of the hospitals’ consultant physicians/unit head who will have primary responsibility for their management. Management protocols will be agreed upon between the medical team and study team. Decisions about intubation, requirement of blood and blood products, transfer of patients to intensive care, weaning of ventilation and extubation will be made by the medical team independently of study doctors. All decisions will be based on the patient’s clinical condition and the available hospital resources, as per usual hospital practice. The study team preferably by trial physicians will note down the record in the patient’s case record form (CRF).

**Prohibited Medications:** No medicines are specifically prohibited for this clinical trial.

**Non-investigational medicinal products:** All patients will receive standard care plus supporting care according to the “National Guidelines on Clinical Management of Coronavirus Disease 2019 (COVID-19)”. Among the standard care fluids, oxygen, ventilatory support, and antipyretics will be provided as necessary in all Arms of patients and will be decided by the chief/consultant of the admission unit. No other noninvestigational product will be used for the study purpose. In case of any product required for the best suited management, inclusion of this patient will be decided upon the opinion of the PI.

**Methods of data collection:** Data collection will be performed by the trial physicians. A paper based semi-structured questionnaire will be made and pretested before data collection. All potential participants will be recorded in this database at first contact and assigned a study number. This study number (e.g., DMC-PVP-I-0001) will be used for all data and samples collected from that person. Study doctors will recruit and randomize patients. They will not be able to predict allocation before randomization. Following randomization, allocation will be performed by the PI, and trial physicians or nurses will confirm the administration of either drug (0.4% or 0.5% or 0.6% PVP-I)/placebo (distilled water). Patients will be closely monitored. Temperature will be measured every 6 hours, and blood pressure, respiratory rate, and pulse rate will be measured every hour. Urine output will be measured in every 8 hours. Drug-related side effects or any adverse events will be observed in each group.

If there is no reaction or unusual event, another RT-PCR sample will be collected from the nasopharynx and sent for further testing.

The total duration of the follow-up will be 2 days (or a person fulfills the discharge criteria). All clinical events will be noted in case record form by trial physicians, including vital status at hospital discharge. Data entry will be date/time stamped. Laboratory analysis data will be collected using the same CRF.

**Data quality and standards:** Following collection, all data sets and collected record forms will be checked. A formal clinical data management plan will be written before the study starts, agreed upon by the co-investigators and Data Monitoring Committee, and documented as a trial master file. Laboratory results will be discussed regularly between the PI and laboratory managers.

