**Research Hypothesis:**

**Null hypothesis:** Administration of nasal preparations of povidone-iodine (PVP-I) is no longer effective in clearing COVID-19 virus located on the mucosal surface of the nasopharynx.

**Alternative Hypothesis:** Nasal preparations of povidone-iodine (PVP-I) can effectively clear COVID-19 virus located on the mucosal surface of the nasopharynx.

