**Investigational medicinal product and placebo:**

**Intervention for Arms 1, 2, 3, 4 and 5 (PVP-I group/treatment group):** Arm 1 will receive povidone iodine (PVP-I) nasal irrigation at a concentration of 0.4%, Arm 2 will receive povidone iodine (PVP-I) nasal irrigation at a concentration of 0.5%, Arm 3 will receive povidone iodine (PVP-I) nasal irrigation at a concentration of 0.6%, Arm 4 will receive PVP-I nasal spray at a concentration of 0.5% and Arm 5 will receive PVP-I nasal spray at a concentration of 0.6%. The contact time will be minimum 30 seconds.

**Intervention for Arms 6 and 7 (placebo comparator):** Arm 6 (Placebo comparator group) will receive nasal irrigation with distilled water, and Arm 7 (Placebo comparator group) will receive nasal spray with distilled water for the same duration as a placebo agent.

All groups of patients will receive standard medical care according to country guideline.

**Preparation of placebo:** As this study will be an open label study, no blinding will be performed and no dummy placebo will be made.

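### The PVP-I solutions are diluted in normal saline but the controls are distilled water, so an active-control difference cannot be attributed to povidone iodine alone

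*Protocol*

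**What the plan says.** In the protocol, under Dosing regimen, the paragraph on Arms 1 to 5 says of the PVP-I solution: "Proper dilution with normal saline will be added, which will be physically and chemically stable for 6 hours".

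The controls are described differently. Under Investigational medicinal product and placebo, the irrigation control is given as follows: "Arm 6 (Placebo comparator group) will receive nasal irrigation with distilled water". The spray control has the same fluid; its description reads: "Arm 7 (Placebo comparator group) will receive nasal spray with distilled water for the same duration as a placebo agent". The Patients and Methods summary in Part A, Procedure of randomization, Dosing regimen and Methods of data collection also name distilled water as the control fluid.

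Dosing regimen matches the controls to the active arms on quantity, time and rate: "Control groups, will receive distilled water irrigation and distilled water nasal spray at similar amounts and durations". It adds that each control is "a placebo that will also be reconstituted and applied at the same rate as mentioned in the invention groups", without naming what it would be reconstituted with. The product section also states: "As this study will be an open label study, no blinding will be performed and no dummy placebo will be made".

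The General Objective asks about the efficacy of povidone iodine against virus in the nasopharynx. The alternative hypothesis is worded a little more widely: "Nasal preparations of povidone-iodine (PVP-I) can effectively clear COVID-19 virus located on the mucosal surface of the nasopharynx".

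**The concern.** A placebo control should differ from the active product only in the active ingredient. Here two things change together, the iodine and the fluid that carries it. Within an active-control comparison the two are completely aliased: every patient with iodine also has saline, and every patient without iodine has distilled water. No analysis of that comparison can divide an observed difference between them.

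The outcome is measured close to the fluid exposure. Dosing regimen describes 10 ml of PVP-I or distilled water given over 2 minutes, with the repeat RT-PCR 1 to 15 minutes after the intervention. One job of the control arm is to remove the effect of putting fluid into the nose shortly before swabbing. It does this cleanly only if the fluid is the same. The second secondary objective, adverse events among the groups, is exposed in the same way: any difference in how the two fluids are tolerated would be counted for or against iodine.

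**Working it through.** **1. Vehicle by arm, as written.**

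| Arms | Route | PVP-I | Fluid named |
| --- | --- | --- | --- |
| 1, 2, 3 | irrigation | 0.4%, 0.5%, 0.6% | normal saline |
| 4, 5 | spray | 0.5%, 0.6% | normal saline |
| 6 | irrigation | none | distilled water |
| 7 | spray | none | distilled water |

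There is no row with saline and no PVP-I, and none with PVP-I in distilled water.

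**2. Comparisons affected.** The natural route-matched comparisons are 3 for irrigation (Arms 1, 2, 3 against Arm 6) and 2 for spray (Arms 4, 5 against Arm 7). That makes 3 + 2 = 5, each 27 against 27. The protocol's analysis section does not list its comparisons, so the count of five is inferred from the arm structure. Pooling across routes gives 5 × 27 = 135 against 2 × 27 = 54, with the same vehicle difference.

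**3. Comparisons not affected.** Arms 1, 2 and 3 share a diluent, as do Arms 4 and 5. Differences between concentrations within a route are largely free of the problem.

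**4. How much of the active solution is saline.** For simple dilution of a stock of strength s to concentration c, the share is 1 − c/s. The protocol gives no stock strength for the study product; it says the solution is specially prepared. Two assumed stocks show the range:
- s = 10% (the usual skin solution mentioned under Operational definitions): 1 − 0.4/10 = 0.96, 1 − 0.5/10 = 0.95, 1 − 0.6/10 = 0.94.
- s = 1%: 1 − 0.4/1 = 0.60, 1 − 0.5/1 = 0.50, 1 − 0.6/1 = 0.40.

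The share shows that the diluent is a substantial part of what is given under either assumption. It does not measure a bias, and the point does not depend on it.

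**5. What a vehicle effect could do.** The only outcome scale with figures is the one in the sample size section. Its own figure reproduces: n per group = 2 × [σ(1.96 + 0.84)/difference]² = 2 × (10 × 2.80/5)² = 62.72, rounded up to 63, and 2 × 63 = 126. With SD 10 and 27 per arm, the standard error of a difference is 10 × √(2/27) = 2.72. Suppose iodine did nothing and the diluent alone shifted the mean by v. A two-sided 5% test would then reject with probability 1 − Φ(1.96 − v/2.72) + Φ(−1.96 − v/2.72):

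| Assumed shift v | Rejection rate |
| --- | --- |
| 0 | 5.0% |
| 1 | 6.6% |
| 2 | 11.4% |
| 2.5 | 15.1% |
| 5 | 45.1% |

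The shifts are assumptions, and the protocol does not tie this scale to a named endpoint. The table shows only how a diluent effect, if there were one, would be read as an iodine effect.

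**The case against.** **The trial is open label and openly makes no dummy placebo.** True, but this gives up blinding only. A matched vehicle protects against confounding whether or not anyone is blinded.

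**The control may contain saline too, because it is also reconstituted.** The phrase fits plain distilled water poorly, so the protocol is unclear here. But it names no diluent, and every description of the control fluid says distilled water, which remains the natural reading. If saline was intended, the descriptions conflict and still need correcting.

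**The hypothesis speaks of nasal preparations, and preparation versus water is a coherent test of that.** This stands as far as the hypothesis goes. It does not meet the General Objective, which names povidone iodine itself, nor the placebo label on the controls.

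**The concentration comparisons bear on iodine directly.** This also stands in part, so it would go too far to infer that nothing in the trial can inform on iodine. But the range is narrow (0.4% to 0.6% for irrigation, 0.5% to 0.6% for spray), and similar results across it would leave open whether iodine or vehicle caused a difference from control.

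**No harm is shown.** Correct. A reader might infer that the control is biased in favour of PVP-I, or against it. The protocol contains nothing on how saline or water affects swab yield, RT-PCR or tolerability, so neither inference is supported.

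**Conclusion.** The concern holds as a flaw of attribution. As written, all five route-matched active-control comparisons (27 against 27 each), and any pooled version, differ in vehicle as well as iodine, and no arm isolates the vehicle. A difference in RT-PCR result or adverse events would support a statement about PVP-I in saline against distilled water, and not the statement about povidone iodine that the General Objective calls for.

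The size and direction of any diluent effect are unknown, and the effect may be nil. The conclusion rests on two readings: that the saline sentence applies to all five PVP-I arms, as its heading says, and that the controls are plain distilled water, as every description of them says.

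**What to change.** State the vehicle for every arm, and make it the same in the active and control arms of each route. Bring these sections of the protocol into agreement: Patients and Methods in Part A, Procedure of randomization, Investigational medicinal product and placebo, Dosing regimen, and Methods of data collection. In Dosing regimen, say what reconstituting the control means or delete it. The choice of vehicle belongs to the sponsor.

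If the vehicles are to stay different, limit the stated comparison and the conclusion to PVP-I in normal saline versus distilled water, for efficacy and for adverse events.

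The cost before enrolment is a minor amendment. The protocol says ethical clearance has been obtained, so the change goes back to that committee. Changing the control fluid is the lighter route. If the active diluent is changed instead, the stated stability must be rechecked, because the 6-hour figure in Dosing regimen is given for dilution in saline. The Storage section allows use within 48 hours of mixing, and the two statements need reconciling in any case. For patients already treated with unmatched fluids the confounding cannot be undone, and only the limited conclusion remains.

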**Patients and Methods:** This open-label randomized clinical trial will be conducted at the Department of Otorhinolaryngology and Head Neck Surgery in collaboration with the Department of Virology and Department of Medicine in Dhaka Medical College Hospital (DMCH). The study will be conducted from September 2020 to December 2020. A total of 189 confirmed cases of COVID-19 disease proven by reverse transcription polymerase chain reaction (RT-PCR) testing will be enrolled in this study. Written informed consent will be ensured before participation. In case of no literacy, fingerprint will be considered for written permission. Consent will be sought from the legal guardian in case of minor or underaged. Formal ethical clearance will be obtained from the Ethical Review Committee (ERC) of Dhaka Medical College (DMC). All of the participants will be divided into seven Arms: Arm 1 will receive povidone iodine (PVP-I) nasal irrigation at a concentration of 0.4%, Arm 2 and Arm 3 will receive 0.5% and 0.6%, Arm 4 will receive PVP-I nasal spray at a concentration of 0.5% and Arm 5 will receive 0.6%. Arm 6 (placebo comparator group) will receive nasal irrigation with distilled water (DW), and Arm 7 (placebo comparator group) will receive nasal spray with distilled water. The contact time will be minimum 30 seconds. After the individual application of PVP-I and distilled water in the respective participants, they will be tested again for RT-PCR for COVID-19 from nasopharyngeal samples. All patients will be subjected to a detailed history, physical examination and adverse events. Computer generated randomization sequence will be followed for randomization. Data will be recorded in a semi structured questionnaire and will be analyzed by ‘R-4.0.2’ data analysis software.

**Conclusion:** It is expected that the study will reveal the virucidal activity with optimal contact time and concentration of nasal preparations of PVP-I against COVID-19. The results may help in prevention strategies for the general population, health care workers and COVID-19-positive patients.

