**Exclusion criteria:**

- Patients with known sensitivity to PVP-I aqueous antiseptic solution or any of its listed excipients
- Previously diagnosed thyroid disease
- Patients with chronic renal failure: stage ≥3 by estimated glomerular filtration rate (eGFR) Modification of Diet in Renal Disease (MDRD)
- Patients with acute renal failure (KDIGO ≥stage 2: creatinine ≥2 X baseline)
- Pregnant and lactating mother
- Current requirement for invasive or noninvasive ventilation or planned within the next 6 hours.

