**Ethical consideration:**

The researcher is duly concerned about the ethical issues related to the study. In this study, the following criteria will be followed to ensure maintaining ethical values. All ethical measures will be followed in accordance with the current Declaration of Helsinki and Good Clinical Practice (GCP) guidelines.

1. Formal ethical clearance was taken from the ethical review committee of the Dhaka Medical College for conducting the study.
2. Confidentiality of the person and the information will be maintained, observed and unauthorized persons will have no access to the data.
3. Informed written consent will be obtained from the subject.
4. The content of the consent requirements will be as such:
   - 1. Explanation of the nature & purpose of the study.
     2. Explanation of the procedure of study.
     3. Explanation that they have the right to refuse, accept & withdraw to participate in the study.
5. It will be clear to the patient that his/her confidentiality will be maintained, that there is no monetary benefit of the patient in this study, he/she can refuse to participate in the study at any time and it will in no way hamper his/her treatment.
6. It will be made clear to the patient that there is an invasive procedure that will be performed for the study, mostly for the sample collection of RT-PCR.
7. They will be assured that any adverse reaction or unusual events will be managed immediately, with highest care.

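### The restart rule makes no exception for signs of anaphylaxis, and one section makes the outcome swab conditional on no reaction while two others require it without condition

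*Protocol*

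**What the plan says.** **Restart.** In the Overdose paragraph under Dosing regimen, the spray or irrigation is halted for significant discomfort "or clinically significant hypotension or signs of anaphylaxis". The next sentence is "Procedures will be started again at a lower rate if the condition settles or according to the patient", and it closes with the patient's choice.

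Other sections that bear on this:
- Exclusion criteria: "Patients with known sensitivity to PVP-I aqueous antiseptic solution or any of its listed excipients".
- Responsibility sharing of care of the patients: the hospital consultants have "primary responsibility for their management".
- Ethical consideration: participants are assured that "any adverse reaction or unusual events will be managed immediately, with highest care".

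**Outcome swab.** Three sections describe the RT-PCR after application:
- Patients and Methods (Part A): after application, "they will be tested again for RT-PCR for COVID-19 from nasopharyngeal samples".
- Dosing regimen: "Further RT-PCR will be assessed within 1 minutes to 15 minutes of the following intervention".
- Methods of data collection: "If there is no reaction or unusual event, another RT-PCR sample will be collected from the nasopharynx".

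The Proposed Analysis Plan foresees both an intention-to-treat and a per-protocol analysis. The paragraph on preparation of placebo says that there is no blinding.

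**The concern.** The first matter is safety. A protocol that names anaphylaxis as a possible event should give a safe instruction for it. This one gives a single restart rule for three very different halt reasons. A patient whose first anaphylactic sign appears during the application could, in line with the written rule, be exposed to povidone iodine again.

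The second matter is the outcome. The general objective is virucidal efficacy in the nasopharynx, and the swab after application is how clearance is measured. If that swab depends on the absence of a reaction, outcomes are missing because of something that happens after randomisation. Povidone iodine and distilled water may well differ in how often they provoke a reaction. Staff who know the arm decide what counts as a reaction or an unusual event, and the protocol does not define the latter. The compared groups would then no longer be the randomised groups.

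**Working it through.** **Part 1: restart rule.** The two sentences of the Overdose paragraph, read together:

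| Halt reason | Condition for restart | Exception stated |
| --- | --- | --- |
| Significant discomfort | It settles, or the patient chooses | None |
| Clinically significant hypotension | It settles, or the patient chooses | None |
| Signs of anaphylaxis | It settles, or the patient chooses | None |

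The two conditions are joined by *or*, so the patient's choice is enough by itself. Could another section close the gap?
- Exclusion criteria act at entry and cover only sensitivity already known. A first reaction in the trial is outside them.
- The withdrawal rules are led by the participant. They give staff no duty to stop.
- The sections on shared responsibility and on ethics provide for care. Neither forbids a restart.
- Participant compliance speaks of interruption only, and aims to see that every recruited patient receives the intervention.

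Nothing bars re-exposure. Five of the seven arms receive povidone iodine, so the gap concerns 5 × 27 = 135 planned patients.

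**Part 2: swab.** Two sections require the repeat test without condition, and Dosing regimen adds the window of 1 to 15 minutes. Methods of data collection attaches a condition and does not say what happens when it fails. Omission is implied, not stated. No later sample for patients who react is described anywhere.

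**Part 3: size.** Input: 27 patients per arm in 7 arms (Number of participants). Check: 7 × 27 = 189, as stated.

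If *m* swabs are missing in an arm and *x* of the 27 − *m* swabbed patients have cleared, the clearance rate of the full arm lies between *x*/27 (none of the missing cleared) and (*x* + *m*)/27 (all cleared). The width is *m*/27, whatever *x* is:
- *m* = 1: 1/27 = 3.7 points
- *m* = 2: 2/27 = 7.4 points
- *m* = 3: 3/27 = 11.1 points

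Example with assumed counts: 17 of 24 swabbed patients cleared and 3 were not swabbed. The observed rate is 17/24 = 70.8%. The bounds for the full arm are 17/27 = 63.0% and 20/27 = 74.1%.

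For a difference between two arms the widths add. With 3 lost in one arm and 1 in the other, the width is (3 + 1)/27 = 14.8 points.

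The bias in one arm's observed rate is *r* × (*p* swabbed − *p* unswabbed), where *r* is the share not swabbed. The protocol gives neither *r* nor the gap between the two rates, so neither sign nor size follows. If the two rates are equal, the bias is zero.

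**The case against.** **On the restart.** The application is short: 10 ml over 2 minutes, or two sprays in each nostril, with no schedule of repeat dosing. Restart matters only if the reaction begins within that time. Management is to be agreed between the medical and study teams and based on the patient's condition, so clinical judgement surrounds the rule. This is fair, and it limits how often the rule would apply. It does not remove the gap, since a physician who refused to re-expose the patient would be departing from the written text.

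A reader might infer that hypotension also calls for a permanent stop. The protocol does not support that. In acutely ill inpatients hypotension may come from the illness, and the plan is to adjust the procedure against it.

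**On the swab.** The conditional sentence follows directly on the observation of side effects and may be meant only as a safety check before swabbing. That is possible, but the sentence provides no later sample. It could also be read as describing a sample additional to the one at 1 to 15 minutes, in which case no outcome is lost. That reading is strained, because no second sample after application is described anywhere else.

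A reader might also infer that the condition contradicts the intention-to-treat plan. It does not. Intention-to-treat means analysis by assigned arm and does not promise complete outcomes. How missing swabs are handled may properly be left to the statistical analysis plan. What stands is that the condition creates missing outcomes that no analysis rule can fully repair.

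**Conclusion.** Both parts hold. The restart rule is unsafe as written, because it covers signs of anaphylaxis and nothing elsewhere in the protocol overrides it. The condition on the swab is inconsistent with the two unconditional statements. If it is followed, patients who react lack the clearance outcome, and the intention-to-treat analysis is weakened rather than contradicted.

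The size rests on the planned 27 per arm: 3.7% of an arm for each lost swab. A reader might infer that the result is biased in favour of povidone iodine. The document does not support that, because it gives no reaction rate and no clearance rate in patients who react. Nor does it show that any clinician would in fact re-expose a patient after anaphylaxis. The finding is about what the written rules permit.

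**What to change.** **Overdose paragraph.** State that any sign of anaphylaxis means permanent discontinuation of the study procedure. After discomfort or hypotension, allow a restart only if the condition has resolved, the treating physician decides on it and the patient agrees. Patient choice alone should not be enough.

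**Methods of data collection.** Delete the condition. Take the nasopharyngeal swab at 1 to 15 minutes from every participant who has not withdrawn from study procedures or, after a reaction, as soon as clinically safe. Record the actual time. Report missing and late swabs by arm, with the reason. This respects the withdrawal options, one of which already lets a participant stop the study medication and continue with study procedures.

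**Cost.** Wording in two places, with no extra patients or tests. Some swabs from patients who react will fall outside the 15-minute window, and a few may still be missing. A late swab, or one after a halted application, does not measure quite the same effect, which is why the time must be recorded.

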**Secondary objectives:**

1. To determine the efficacy of povidone iodine in clearing COVID-19 virus located in the nasopharynx
2. To assess the adverse events among the groups

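### Adverse events are compared between unmasked arms under a rule that allows either an attributed or an all-cause count, with no timed or elicited nasal assessment, so the comparison is open to differential ascertainment.

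*Protocol*

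**What the plan says.** The second item under Secondary objectives is "To assess the adverse events among the groups". Preparation of placebo, under Investigational medicinal product and placebo, states "As this study will be an open label study, no blinding will be performed and no dummy placebo will be made". Under Methods of data collection, "Data collection will be performed by the trial physicians", and trial physicians or nurses also confirm whether povidone iodine or distilled water was given.

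The adverse-event rule in that section is "Drug-related side effects or any adverse events will be observed in each group". The same paragraph schedules temperature every 6 hours, blood pressure, respiration and pulse every hour, and urine output every 8 hours. The text that follows sets a follow-up of 2 days (or until discharge criteria are met) and has the trial physicians enter every clinical event on the case record form.

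Three other places bear on the point:

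- Part A, Patients and Methods, promises every patient a history, an examination and adverse-event assessment, without times or content.
- Dosing regimen, in the paragraph on the intervention arms, mentions "monitoring of vital statistics, in case of bleeding protective measures will be performed according to the national guidelines". The paragraph on the control arms has no such wording.
- Overdose, under Dosing regimen, says "Nasal spray and nasal irrigation will be halted if patients complain of significant discomfort", and names hypotension as the key adverse effect.

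**The concern.** The rule names two different counts. A count of drug-related effects needs a causality judgement, made here by staff who can know the arm, and Arms 6 and 7 receive no active drug to which an event could be attributed. A count of all adverse events needs no such judgement. Two physicians could apply the sentence differently and both comply with it.

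The scheduled measurements do not detect local nasal reactions. Whether such a reaction is recorded then depends on who asks, what is asked and when. In an open-label trial all three may vary with the arm. If they do, the recorded difference mixes a treatment effect with a recording effect, and no later analysis can recover symptoms that were never elicited.

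**Working it through.** **1. What is counted.** Set the two statements under Methods of data collection side by side. The monitoring sentence allows drug-related effects or any adverse events. The follow-up text has every clinical event noted. The second supports an all-cause count, but it does not withdraw the attributed alternative. It also does not say which count is used for the between-group objective.

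**2. When and how local reactions are looked for.**

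| Source in the protocol | Applies to | Time fixed? | Local nasal item? |
|---|---|---|---|
| Temperature, vital signs, urine output | patients, no arm restriction | yes | no |
| History and examination (Part A) | all patients | no | none stated |
| Clinical events on the case record form | no arm restriction | within follow-up only | none stated |
| Semi-structured questionnaire | participants | no | content not shown |

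No row combines a fixed time with a local nasal item.

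**3. What differential recording would do (illustration only).** The protocol gives no adverse-event rate, so there is no stated figure to reproduce. Only the arm size comes from the document: 27 per arm, hence 5 × 27 = 135 on povidone iodine and 2 × 27 = 54 on water. All event rates and recording probabilities below are assumptions.

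Recorded rate = true rate × probability of recording, so

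apparent risk ratio = true risk ratio × (recording probability under povidone iodine ÷ recording probability under water).

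- True rate 20% in both, recorded 90% v 50%: 0.20 × 0.90 = 18% and 0.20 × 0.50 = 10%. Apparent ratio 0.90 ÷ 0.50 = 1.8, true ratio 1.0.
- Recorded 90% v 60%: 0.90 ÷ 0.60 = 1.5.
- Recording reversed, 50% v 90%, with a true ratio of 1.8: true rates 0.20 × 1.8 = 36% and 20%, recorded as 0.36 × 0.50 = 18% and 0.20 × 0.90 = 18%. A real excess disappears.

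The probability of a nominally significant false excess on povidone iodine uses the usual two-proportion approximation, Φ[(p₁ − p₀ − 1.96 × SE₀) ÷ SE₁]. SE₀ is the standard error from the pooled rate and SE₁ the one from the separate rates. For 18% v 10% with 27 per arm:

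- SE₀ = √(2 × 0.14 × 0.86 ÷ 27) = 0.0944
- SE₁ = √[(0.18 × 0.82 + 0.10 × 0.90) ÷ 27] = 0.0938
- (0.08 − 1.96 × 0.0944) ÷ 0.0938 = −1.12, which gives 13%

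The nominal value in that direction is 2.5%. Results over the range of assumptions:

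| Assumed true rate | Recording | 27 v 27 | 135 v 54 |
|---|---|---|---|
| 10% | 90% v 60% | 6% | 8% |
| 20% | 90% v 50% | 13% | 25% |
| 40% | 90% v 50% | 25% | 58% |
| any of these | equal | 2.5% | 2.5% |

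With equal recording the problem vanishes, which is what a uniform rule aims at.

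**The case against.** The strongest defence is that the protocol covers more than its one sentence suggests. Read naturally, any adverse events in each group is inclusive, and the follow-up text confirms it by having all clinical events recorded. Every patient has a history and an examination. The second swab is taken only if no reaction or unusual event has occurred, which implies some look for reactions after application in every arm. The effect that the protocol itself calls key, hypotension, is captured by hourly blood pressure. Symptom items may sit in the questionnaire or the case record form, which are not shown. Open label is a declared choice.

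Much of this stands, and it rules out three stronger readings:

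- A reader might infer that local reactions are counted only when the patient complains. The complaint wording under Overdose governs when the procedure is halted. It is not a counting rule.
- A reader might infer that controls are monitored less, because Dosing regimen mentions monitoring only under the intervention arms. The section on the investigational product gives standard care to all groups, and Methods of data collection sets the monitoring schedule without distinguishing arms. The Dosing regimen text needs reconciling with these, but it does not show closer observation of one side.
- A reader might infer that the comparison is biased. The protocol does not establish that.

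The defence leaves a gap, however. None of these passages fixes a time, a local-symptom item or a causality rule, and none says that the questioning is the same in every arm. An unseen form cannot settle the wording of the protocol's own rule. Open label makes a uniform rule more necessary.

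**Conclusion.** The point holds in a limited form. For a declared between-group objective, staff who can know the arm observe events under wording that allows two different counts, and no timed or elicited local nasal assessment is specified. The comparison is open to differential ascertainment of unknown size and direction. The figures above (apparent ratios of 1.5 to 1.8 with no true difference, and a 6% to 58% chance of a false excess) rest wholly on assumed event rates and recording probabilities. They show what could happen and are not estimates for this trial. This weakens the adverse-event comparison and is worth correcting before recruitment, because it concerns bedside data collection. It does not make that objective unanswerable.

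**What to change.** Under Methods of data collection, replace the adverse-event sentence with one rule for all seven arms:

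- The trial physician asks the same fixed local-symptom checklist at the time of the post-application swab (including when a reaction means that the swab is not taken) and again at the end of follow-up.
- Every event is recorded whatever its suspected cause.
- The between-arm comparison uses all events. Relatedness is recorded separately and reported as a secondary listing only.

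The cost is one short checklist on the case record form, completed by physicians already collecting the data. The downside is that solicited questions raise the number of mild events recorded in every arm.

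Separately, reconcile the intervention-arm paragraph of Dosing regimen, which mentions vital-sign monitoring, with the sections that apply care and monitoring to all patients. That sentence also covers clinical care, so how it should read is for the investigators to settle. No clinical care is proposed here.
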